### **Notification by GPs**

GPs are asked to contact the Study Office if the participant moves, becomes too ill to continue or dies, or any other notifiable or adverse event occurs. Alternatively, staff at the Study Office may contact the GP.

### **Offices for National Statistics (HES [Hospital Episode Statistics] data in England, ISD [Information Statistics Division] data in Scotland)**

Consent will be sought from all participants to trace their medical records and addresses from local records and centrally held computerised databases. This should facilitate long term follow up.

### **Ethical arrangements**

We believe the proposed research does not pose any specific risks to individual participants nor does it raise any extraordinary ethical issues.

## **5. DATA COLLECTION AND PROCESSING**

Follow up will continue for 24 months from the date of randomisation including those who agreed to enter the non-randomised cohort whilst that part of MASTER was open (up to and including 27 Oct 2015). It is not part of this protocol or the current study to follow up the men beyond this time. However, consent will be sought to make this possible in the future, and long term follow up is planned.

### **5.1 Proposed outcome measures**

The outcomes are similar to those piloted and used successfully in MAPS, with the addition of relevant surgical outcome measures. The primary outcome uses the ICIQ-UI Short Form (SF).

#### **5.1.1 Primary outcome measures**

1. The primary clinical outcome is participants' report of UI at 12 months measured by a response indicating any loss of urine to either of the two questions: "How often do you leak urine?" and "How much urine do you leak?" in the validated ICIQ-SF ([name] 2006).
2. The primary economic outcome measure of cost effectiveness is incremental cost per QALY at 24 months based on responses to the EQ-5D™ (EuroQol Group, 1990).

#### **5.1.2 Secondary outcome measures**

##### *General*

- immediate and late post-operative morbidity; blood loss;
- complications related to devices eg urethral erosion or infection;
- other adverse effects or complications;
- operating time;
- length of hospital stay;
- number of readmissions to hospital;
- time until resumption of usual activities;
- need for further surgery for urinary incontinence;

- time to further surgery;
- satisfaction with treatment (ICIQ-satisfaction)

#### *Urinary outcomes*

- urinary incontinence (ICIQ-UI SF Score and types of incontinence)
- use of pads;
- 24-hour pad test (weight of urine lost);
- lower urinary tract symptoms (frequency, nocturia, urgency, and voiding symptoms such as slow stream and hesitancy (ICIQ-Male Lower Urinary Tract Symptoms [MLUTS])).

#### *Sexual function outcomes*

- sexual function (ICIQ-MLUTSsex)

#### *Quality of life outcome measures*

- condition-specific quality of life measures (incontinence from ICIQ-UI SF, and sexual from ICIQ-MLUTSsex)
- general health measures (SF12 and EQ-5D).6TM

#### *Economic outcome measures*

- need for alternative management for incontinence or voiding dysfunction (e.g. PFMT; further surgery; use of pads, drugs, or sheath, indwelling or intermittent catheters);
- cost and use of NHS services;
- cost to the participants and their families/carers;
- QALYs estimated from the responses to the EQ-5D6 TM
- the incremental costs, QALYs and incremental cost per QALY derived by the economic model over a longer term time horizon.

In addition, all participants who have surgery (including non-randomised men who entered the NRC whilst it was open) will be asked to consent to long term follow up, including use of computerised NHS records and other routine data sources.

### **5.1.3 Measurement of outcomes (Table 1)**

Outcomes will be assessed by participant-completed questionnaires and 3-day urinary bladder diaries at baseline, 6, 12 and 24 months. The 24-hour urinary pad test will be used at baseline as an objective assessment of urine loss, measured by pad weighing in grams per 24 hours. The research nurse and/or urologist will complete a CRF at the time of surgery providing details of the operative procedures, complications and resource use in hospital. At 12 months the randomised men will also have a review appointment with their urologist and/or research nurse to evaluate the results of surgery (including another 24 hour pad test), and to identify problems or the need for other treatment. This may occur via the phone if participants have already been discharged by the local centre before this date or pads weighed at a non-research centre closer to their home (provided the equipment used to do this is sufficiently accurate)

Economic outcomes will be assessed using standard economic methods plus trial-specific data collection described earlier. We are using standardised outcome instruments developed by the International Consultation on Incontinence (ICI) for urinary and sexual symptom ([name] 2006). The components and timing of follow-up measures are shown in Table 1.

**Table 1 Measurement of outcomes: components and timing**

|                                    | Baseline | Peri-operative | 6-months | 12-months | 24-months | Long term |
|------------------------------------|----------|----------------|----------|-----------|-----------|-----------|
| CRF                                | ●        | ●              |          | ●*        |           |           |
| ICIQ-UI Short Form                 | ●        |                | ○        | ○         | ○         |           |
| ICIQ-MLUTS                         | ●        |                | ○        | ○         | ○         |           |
| ICIQ-satisfaction                  |          |                | ○        | ○         | ○         |           |
| ICIQ-MLUTSsex                      | ●        |                | ○        | ○         | ○         |           |
| 24 Hour Pad Test                   | ●        |                |          | ●*        |           |           |
| SF12                               | ●        |                | ○        | ○         | ○         |           |
| EQ-5D  ™               | ●        |                | ○        | ○         | ○         |           |
| Further surgery                    |          |                | ○        | ●         | ○         |           |
| Resource utilisation questionnaire | ●        |                | ○        | ○         | ○         |           |
| Urinary bladder diary              | ●        |                | ○        | ○         | ○         |           |
| HES / ISD data                     |          |                |          |           |           | ◇         |

● Clinic/Hospital

○ Postal

◇ Routine data sources

\*For randomised participants only

## 5.2 Questionnaires and Case Report Forms (CRFs)

### 5.2.1 Questionnaires for participants

Participants will be asked to complete a baseline questionnaire and diary before surgery. Content will include:

- Health care utilisation questions (including GP consultations and hospital visits/admissions, use of other services)
- Personal costs (pad use, catheter use, over-the-counter medication, other health care services)
- EQ-5D™
- urinary symptoms (ICIQ-MLUTS, urinary leakage ICIQ-UISF, and effect on QOL ICIQ-qol, [www.iciq.net/](http://www.iciq.net/))
- sexual symptoms (ICIQ-MLUTSsex <http://www.iciq.net/ICIQ.MLUTS.html>)

The follow up questionnaires and diaries at 6, 12 and 24 months will repeat the baseline questions and in addition will enquire about:

- Complications and adverse effects
- Need for further treatment for incontinence or complications, including further surgery.

The follow up questionnaire at 12 and 24 months will repeat the questions and in addition will enquire about:

- Satisfaction with surgery results and willingness to recommend to a friend.

### 5.2.2 Urinary diaries

Participants will be asked to complete urinary diaries at each questionnaire time point, including frequency of micturition, leakage and nocturia, use of pads and wetting of clothes.

## **Case Report Forms (CRFs)**

### **5.2.3 Baseline CRF**

At baseline, the Urologist and/or Research Nurse will complete a CRF with the following content:

#### **Pre-operative**

- i) Contact details, GP address, phone numbers
- ii) Urological and surgical history
- iii) Urodynamics
- iv) Pad tests

#### **Intraoperative**

- i) Intraoperative data including date of admission and operation
- ii) Operative procedures and theatre time
- iii) Catheter use
- iv) Complications

#### **Postoperative**

- i) Pain relief, infection, haematoma, other complications
- iii) Date of discharge

### **5.2.4 12 Month Clinical Review Assessment Form**

At 12 months after surgery, all men will be reviewed by the urologist and/or the research nurse

- i) Clinical findings (pad tests)
- ii) Complications and adverse events

### **5.2.5 Serious Adverse Event (SAE) Report Form**

Serious adverse events will be coded and recorded using a standard SAE CRF form at the behest of a local Urologist. The SAE form will be used to record details of any serious adverse events related to the incontinence surgery/procedure undertaken as part of MASTER.

## **5.3 HES and ISD Data**

After the last man has been recruited, we will run periodic checks for operations, diagnoses and hospital admissions with centrally collected data, to supplement and validate data collected from the participants, and to set up mechanisms for long-term follow up.

## **5.4 Data processing**

Research Nurses will enter locally-collected data in the centres. Staff in the Study Office will work closely with local Research Nurses to ensure that the data are as complete and accurate as possible. Follow up questionnaires to men will be sent from and returned to the Study Office in Aberdeen. Extensive range and consistency checks will further enhance the quality of the data.

## **5.5 Withdrawal procedures**

Participants may withdraw from any aspect of the trial.

#### **6.1.1 Planned subgroup analyses**

Sub-group analysis according to type of prostate surgery will be considered within the following groups:

- Radical prostatectomy or TURP;
- Amount of urine leaked per 24 hours at baseline, above, and below or equal to 250 grams per 24 hours.

Heterogeneity of treatment effects amongst subgroups will be tested for using the appropriate subgroup by treatment group interactions (Pocock 2002). Stricter levels of statistical significance ( $2P < 0.01$ ) will be sought, reflecting the exploratory nature of these analyses.

All study analyses will be according to a statistical analysis plan that will be agreed in advance by the Trial Steering Committee (TSC) and the Data Monitoring Committee (DMC).

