Currently the male sling is being offered to people seeking treatment with the NHS on a haphazard basis according to surgeon enthusiasm and local arrangements. Both clinicians and patients lack the evidence required to make an informed choice between the two options and NHS policy makers lack information on cost-effectiveness to plan service provision. The recent Cochrane Review, (Silva 2011) highlighted the need for adequately powered comparative randomised controlled trial (RCTs) of the surgical options for these men. The MASTER trial will determine whether patients can be confidently informed about whether implantation of the male sling gives equivalent effectiveness for cure of incontinence to the standard AUS. This will allow patients and their clinicians to make an informed decision regarding the individual suitability of either option, taking into account other factors such as the relative need for subsequent re-intervention, the need to operate a control pump, and speedier recovery. As part of the trial design, we will take into account the different clinical characteristics of the participants, such as type of prostate surgery, and identify factors which may influence comparative effectiveness, such as degree of incontinence. Affected people, clinicians, and the NHS will benefit from the reliable evidence from the trial, to guide the choice of treatment and health care provision decisions, in terms of effectiveness, cost effectiveness and adverse effects.

At present the design and function of the AUS appears optimal, and despite attempts to improve on the existing device there are no signs of significant innovations that would have to be considered prior to or during this trial. Sling technology, however, is less mature and we anticipate that during the trial recruitment period, there may be a choice of implants from differing manufacturers. For that reason we will not specify which brand of male sling should be used. However, it should be of the sub-urethral trans-obturator type, as currently, almost all implanted slings are of this type, and the available outcome data are chiefly for this type of sling. A robust examination of the comparative effectiveness of this new surgical option will provide high quality evidence to determine whether or not it should be adopted widely in the NHS.

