### **3.2 Target population**

People with USI after prostate surgery (radical prostatectomy or TURP), for whom surgery is judged appropriate, are the target population. For the purposes of the trial we will define people with mild incontinence as those not requiring surgery. There is no clear threshold for defining moderate or severe incontinence and no clear evidence of differential benefit for either intervention according to degree of incontinence. We will therefore include all people whose incontinence is considered, from both the patient and surgeon perspectives, to require surgery.

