## **3.8 Sample size**

There is a lack of robust evidence from comparative studies on which to base the trial sample size calculation. For the primary outcome (incontinence), limited evidence from case series suggests that 20% of people would still be incontinent 12 months after AUS. For male slings, after primary implantation the percent of people incontinent is thought to be 35%.

For our chosen non-inferiority comparison at 12 months, a trial with 310 participants will allow us to be 90% sure that the lower limit of a two-sided 95% confidence interval will exclude the possibility that the AUS is more effective by a margin of 15% or more. Allowing for 15% loss to follow-up after enrolment we plan to recruit 180 participants per group into the trial. This sample size will allow the detection of a difference equivalent to 0.25 of a standard deviation (SD) at 80% power between the groups for the key secondary outcome, ICIQ at 24 months.

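### Section 6.1.1 tests whether the treatment effect varies with baseline leakage by cutting a continuous pad weight at 250 g, a cut with no stated basis; a continuous term would use the same data better, though the test would remain underpowered

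*Protocol*

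**What the plan says.** Section 6.1.1 names two subgroup factors: type of prostate surgery, and baseline leakage, split into two groups, "above, and below or equal to 250 grams per 24 hours". Differences in treatment effect are to be "tested for using the appropriate subgroup by treatment group interactions". A significance level of 2P<0.01 "will be sought, reflecting the exploratory nature of these analyses".

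Section 5.1.3 shows that baseline leakage is recorded on a continuous scale, "measured by pad weighing in grams per 24 hours". Section 3.2, explaining why men with any degree of incontinence judged to need surgery are eligible, states: "There is no clear threshold for defining moderate or severe incontinence". The Introduction in section 1 says that the trial will "identify factors which may influence comparative effectiveness, such as degree of incontinence".

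The protocol gives no reason for 250 g, no distribution of baseline pad weight, no expected share of men above the cut, and no power for the interaction.

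**The concern.** The protocol says the trial will look at whether degree of incontinence changes how the two operations compare. For leakage, the interaction in section 6.1.1 is the only planned test that serves this aim. The trial measures leakage in grams, but the test uses only which side of 250 g a man falls on. A man at 251 g is treated like one at 1,000 g and unlike one at 249 g. If the treatment effect changes smoothly with leakage, this throws away information already collected, and the result depends on a cut that the protocol does not justify. A null interaction could then be misread as evidence that the operations compare equally well at all degrees of leakage.

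**Working it through.** **Inputs from the protocol.** Section 3.8: 12-month incontinence of 20% (AUS) and 35% (sling), 310 participants for the primary comparison, 180 per group recruited, 15% loss. Section 6.1.1: cut at 250 g, 2P<0.01.

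**Assumptions, not in the protocol.** 80% power for the interaction; risk-difference scale; a normal moderator (or log-normal on the log scale) with a linear interaction; the share of men in the smaller leakage group, varied below.

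**The plan's own figure.** Section 3.8 says "a trial with 310 participants will allow us to be 90% sure". With a 20% rate in both groups, a 15-point margin and one-sided 0.025, the simple normal formula is 0.32 × (1.960 + 1.282)² / 0.15² = 149.4, so 150 per group or 300 in all. The Farrington-Manning score version gives 153 per group, or 306. Power at 155 per group is 91.0%. The 310 is therefore reproduced closely. After 15% loss, 360 × 0.85 = 306, which is used below (153 per group). There is no stated figure for the interaction to reproduce.

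**Information kept by the cut.** Relative to a linear term, the split keeps the squared correlation between the covariate and its two-group version. For a normal covariate with share p in the smaller group this is φ(z_p)² / [p(1 − p)]. At p = 0.5: 0.3989² / 0.25 = 0.637.

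**Detectable difference with the cut.** The two group variances sum to 0.20 × 0.80 + 0.35 × 0.65 = 0.3875. SE = √{0.3875 × [1/(153p) + 1/(153(1 − p))]}. At p = 0.5: √(0.3875 × 2/76.5) = 0.101. Multiplying by 2.576 + 0.842 = 3.418 gives 0.344.

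**Detectable difference with a continuous term.** SE per SD = √(0.3875/153) = 0.0503; × 3.418 = 0.172, or about 17 points per SD. The means of the two leakage groups lie φ(z_p) / [p(1 − p)] SDs apart. At p = 0.5 this is 1.596, so the same contrast is 17.2 × 1.596 = 27 points.

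| Share in smaller group | Information kept | Lost | SE, cut | Detectable, cut (points) | Separation of group means (SD) | Detectable, continuous, same contrast (points) |
|---|---|---|---|---|---|---|
| 50% | 0.637 | 36% | 0.101 | 34 | 1.60 | 27 |
| 30% | 0.576 | 42% | 0.110 | 38 | 1.66 | 28 |
| 20% | 0.490 | 51% | 0.126 | 43 | 1.75 | 30 |
| 10% | 0.342 | 66% | 0.168 | 57 | 1.95 | 34 |

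**Sensitivity to the outcome variance.** With N = 310, the median-split figure with the cut is 31 points if the variance is 0.16 in both groups and 39 if it is 0.25. Multiplying by √0.637 = 0.798 gives 25 and 31 with a continuous term.

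**Sensitivity to the distribution (simulated).** With an effect linear in the stated scale, the loss is 25% for a uniform covariate cut at its median and 73% at 10:90. On the raw gram scale it is 35% to 90% for an exponential covariate and 43% to 95% for a log-normal one (log SD 0.8 to 1), depending on where the cut falls. It is zero if the effect truly steps at 250 g.

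**A benchmark.** Appendix 1 (A1.3) cites a sling case series with cure or improvement of 82% in mild or moderate and 67% in severe incontinence, a gap of 15 points. That is a different endpoint in an uncontrolled series, so it is only an illustration. Suppose AUS results did not vary with leakage, so that this gap were the interaction at a median split. With the cut, z = 0.15/0.101 = 1.49 and power is Φ(1.49 − 2.576) = 14%. With a continuous term carrying the same gradient, z = 1.49/0.798 = 1.87 and power is 24%.

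**The case against.** The strongest reply is that the analysis is labelled exploratory, is only to be considered, and uses a single prespecified cut, which prevents choosing a threshold from the data. A continuous term brings a choice of functional form. If the effect really stepped at 250 g, the cut would be the efficient test and a linear term would be the one losing information, by the same 36% to 66% under normality. The SAP, not shown, could add a continuous analysis. The sentence in section 3.2 is about eligibility and does not say that a prespecified cut is wrong.

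Most of this stands as a limit on how much the point matters. It does not remove the point. Prespecification prevents data-driven choice but does not make the cut informative, and a continuous term can be prespecified just as well. Nothing in the protocol suggests a step at 250 g, and section 3.2 weakens any claim that it is an established threshold. The cut is fixed in the protocol itself.

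A reader might infer several stronger things that the protocol does not support:

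- **That the cut loses a third to two thirds of the information as a matter of fact.** That range needs the normal or log-normal shape, a linear interaction and 10% to 50% of men in the smaller group. None of these is given.
- **That the 2P<0.01 level is part of the error.** It is a declared choice. It lowers power for either test and has no bearing on the share of information lost.
- **That leakage is the only planned test of effect modification.** The type of prostate surgery is tested too.

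**Conclusion.** The point holds as a minor improvement to an exploratory analysis. A continuous moderator is cut at a value with no stated basis, and under a smooth effect that wastes information. Under a normal (or log-normal on the log scale) moderator and a linear interaction, the loss is about 36% at a median split and about 66% at 10:90. Outside those assumptions it could be anything from zero to 90% or more.

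It would be wrong to infer that a continuous term makes the interaction test informative. At a median split the detectable difference falls only from about 34 to about 27 points (17 points per SD), when the whole difference assumed between the operations is 35% − 20% = 15 points. Sample size is the larger limit, and a null interaction should not be read as similarity of effect under either analysis. The primary non-inferiority conclusion does not depend on this test.

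**What to change.** In section 6.1.1, state that the treatment-by-leakage interaction will be tested with baseline 24-hour pad weight as a prespecified continuous term, for example log-transformed and linear, with a prespecified check of functional form such as a spline. Keep the 250 g groups only to display estimates, and carry the same wording into the SAP. The 2P<0.01 level can stay.

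The change takes one sentence in each document and needs no new data, visits or participants. The cost is that a functional form must be chosen in advance and checked, with about 306 men to check it on, and that a linear term would be less efficient if the effect did step at 250 g.

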#### **6.1.2 Proposed frequency of analyses**

A single main analysis will be performed at the end of the trial when all 24-month follow up has been completed. An independent DMC will review confidential interim analyses of accumulating data at its discretion but at least annually. A major consideration for the DMC will be to monitor the 12 month primary outcome (i.e. the non-inferiority margin).

### **6.2 Economic evaluation**

The trial will include a formal economic evaluation assessing the costs and cost-effectiveness of the interventions compared from the perspectives of the NHS and the participants and their families. Resource-use data collected will include the cost of the intervention and the use of primary and secondary NHS services by the participants, including further referral for subsequent additional specialist management. Health service costs refer to those incurred directly by the NHS due to the surgery and subsequent appointments and procedures. Personal costs to the participants (such as costs of travelling to appointments and work/social restrictions) will also be investigated.

Resource use will be recorded prospectively for every participant within the study. For the surgical interventions, operative details will be recorded at the time of surgery (e.g.

time the surgery takes, the time spent in recovery, grade of surgeon and assistant, grade of anaesthetist). A parallel exercise will establish resources used immediately before, during and after (i.e. in recovery) the operation e.g. other staff, consumables (surgical requisites), and capital (costs associated with using the theatre facilities, costs of using reusable equipment). Costs to the participants will be collected using a questionnaire based on one developed by the UK working party on patient costs. The use of secondary care services (e.g. length of hospital stay, outpatient appointments, and readmission) will be abstracted from patient notes or questionnaires. The use of primary care services, including medications prescribed will be collected using a patient questionnaire. Unit costs/prices will be obtained using published estimates for health care services and/or interventions.

A generic instrument (the EQ-5D™) will be used to measure health state. Trial participants will be asked to complete the EQ-5D™ at baseline and at six, 12 and 24 months after their operation. This instrument will provide the quality of life weights to compute the QALYs.

Incremental cost-effectiveness ratios will be computed comparing the cost of the interventions. The difference in effectiveness will be expressed in terms of the number of participants who are still incontinent at 24 months. These data will be based on responses to either of two questions relating to the loss of urine, retrieved from the participant questionnaires. Incremental cost-utility ratios will be computed comparing the interventions. The difference in utility will be expressed in terms of QALYs at 24 months. Where appropriate, the analysis of incremental costs, effectiveness and cost-effectiveness will be based on similar statistical models as those outlined in the statistical analysis plan above. This 'within' trial analysis will include both deterministic and stochastic sensitivity analyses to explore statistical and other forms (e.g. around unit costs or the source of utility estimates) of uncertainty.

An economic model which considers a longer time horizon will also be developed to provide additional information for policy makers. In the model, the findings of the trial will be extrapolated to the participant's life time. The model will describe care pathways that people may follow and will include the initial surgery and any subsequent treatments. The structure of the model will be developed in collaboration with the expert panel of service users, patients, clinicians and trial collaborators. Parameter estimates for relative effectiveness up to two years, costs and utilities will be derived from the trial data. Data from the trial will be supplemented with data from other sources (e.g. Cochrane review, other future RCTs). These data will be assembled systematically and will follow guidelines for good practice (Philips 2004).

Outcomes in the model will be expressed in terms of an incremental cost per QALY. Parameter uncertainty will be integrated by the incorporation of probability distributions into the model and involve Monte Carlo simulation. Other forms of uncertainty such as that associated with choices made about the structure of the model, discount rate, etc. will be addressed through sensitivity analysis. The base case and sensitivity analyses will be presented as cost effectiveness acceptability curves. The model will also be used to identify priorities for further research by investigating the expected value of information.

